## Abstract

**Background:**

Nutrition counseling before gastrointestinal surgery can improve patients’ quality of life, treatment tolerance, and surgical recovery. Nutrition counseling is especially important for individuals diagnosed with esophageal and gastric cancer, who are at high risk of malnutrition. Despite the increased risk for malnutrition, less than half of individuals diagnosed with esophageal and gastric cancer receive nutrition counseling before surgery. To address this practice gap, the Support through Remote Observation and Nutrition Guidance (STRONG) implementation strategy was developed.

**Methods:**

STRONG includes three theory-informed strategies: an electronic health record order set for a standardized protocol that specifies the timing and amount of nutrition counseling that should be received, collection and visualization of patient-reported nutrition information in a web-based dashboard, and a question prompt list for the patient-dietitian encounter. Patients (*N* = 80) will be 1:1 randomized to STRONG or implementation as usual in this pilot trial. The trial will be pragmatic in design and STRONG will be implemented with existing clinic teams and workflows. The study’s primary aim will be to assess feasibility and acceptability against pre-planned benchmarks and secondary aims include collecting preliminary data on effectiveness and implementation outcomes that will support a future definitive hybrid implementation-effectiveness trial.

**Discussion:**

Pilot studies play a critical role in implementation research by ensuring that strategies and proposed study methods are feasible prior to conducting a definitive trial. Positive findings from this line of research could support definitive testing of a patient-mediated implementation strategy to improve nutrition care access and delivery for cancer patients at high risk of malnutrition.

**Trial registration:**

ClinicalTrials.gov NCT06497569. Registered on July 11, 2024, prior to participant enrollment.

## Background

Studies estimate that most esophageal and gastric cancer patients are diagnosed with malnutrition during cancer treatment [1–6]. The high prevalence of malnutrition is caused by the cancer’s location in the digestive tract and receipt of cancer treatments that affect nutrition [7–10]. Esophageal and gastric cancer patients may experience nutrition-impact symptoms, such as swallowing difficulty, that affect the ability and desire to eat [7, 11, 12]. Patients can also experience problems with digestion, motility, and nutrient absorption [13–15]. Malnutrition has a negative impact on patients’ quality of life, treatment tolerance, and survival and increases caregiver distress and burden [9, 16–24]. At the system level, malnutrition can increase hospital length of stay, readmission rates, and healthcare costs [25–27]. Clinical guidelines recommend that all cancer patients at risk for malnutrition receive nutrition counseling from a registered dietitian [28–32], an evidence-based intervention for improving nutritional status [33, 34]. In practice, access and delivery of nutrition counseling for patients with malnutrition varies across cancer care settings [35–38]. 

Despite the importance of nutrition counseling, studies suggest that less than half of esophageal and gastric cancer patients meet with a dietitian during cancer treatment [39, 40]. Nutrition counseling is particularly important for patients who are receiving surgical treatment. Patients receiving surgical treatment are likely to receive neoadjuvant treatment to prepare for surgery, such as chemotherapy and radiotherapy, which can worsen nutritional status [41–43]. Nutritional status is a key predictor of post-surgical complications and recovery [44–47]. Therefore, intervening on nutritional status prior to surgery is critical for improving patient outcomes. To improve nutrition care delivery prior to surgery, several barriers need to be overcome. First, many cancer care systems lack standardized protocols that specify when dietitian referrals should be made or how much counseling is needed, resulting in late referrals and inadequate follow-up [36, 48–50]. Second, dietitians may lack sufficient patient-reported information, such as nutrition-impact symptoms, that may be important for monitoring malnutrition and tailoring nutrition counseling to the individual patient [48, 51, 52]. Third, patients may not understand the role of the dietitian in cancer care or the potential value of nutrition counseling. Given the many competing priorities cancer patients face, especially early on during cancer treatment, patients may be reluctant to meet with a dietitian when referred [53, 54]. Finally, patients may not have the skills or resources necessary to engage in and adhere to recommendations from nutrition counseling (e.g., tracking dietary goals, food security) [55–60]. To ensure consistent access and delivery of nutrition counseling, implementation strategies are needed to standardize early and ongoing nutrition counseling, integrate patient-reported nutrition information into the clinical workflow, and provide patient-mediated tools to empower patients to actively participate in their nutrition care.

To address this gap, our study team developed Support through Remote Observation and Nutrition Guidance (STRONG), a novel patient-mediated strategy to improve access and delivery of nutrition counseling. The target population is individuals diagnosed with esophageal and gastric cancer who are preparing for surgery. We chose this population given the high burden of malnutrition [1–6] and the potential to deliver nutrition counseling early when impact on patient outcomes may be maximized [44–47]. The long-term goal of this line of research is to improve the quality of nutrition care that cancer patients receive and to reduce the adverse outcomes for patients, caregivers, and cancer care systems that are associated with malnutrition. This manuscript will present the methodology of a pilot randomized controlled trial that compares the STRONG program with implementation as usual. The trial is designed to be pragmatic with broad inclusion criteria and use of existing clinical staff and pathways [61]. The primary aim of the study is to assess the feasibility and acceptability of the STRONG program among esophageal and gastric cancer patients, cancer caregivers, and healthcare providers. A secondary aim is to collect preliminary data on implementation outcomes guided by the RE-AIM (reach, effectiveness, adoption, implementation and maintenance) framework [62] and effectiveness outcomes (patient and service delivery) [63] that may be improved by STRONG. Findings from this pilot study will be used to refine the STRONG implementation strategy and support a future definitive hybrid implementation trial. Further, there has been limited study of patient-mediated strategies within implementation science. To date, most studies have evaluated the impact of patient-mediated strategies on patient outcomes and have not measured the impact on implementation outcomes or service delivery [64–67]. Research from the proposed study will contribute to the literature by advancing our understanding of how patient-mediated implementation strategies affect the implementation and delivery of nutrition care in oncology.

## Methods

### Study setting

The study will be conducted at Moffitt Cancer Center (Moffitt) and the University of North Carolina at Chapel Hill (UNC), two Cancer Centers that serve different patient populations. Moffitt is a standalone, non-profit National Cancer Institute (NCI)designated Comprehensive Cancer Center that serves a primarily urban patient population (93%) in a region of Florida where 21% of the population is Latino/Hispanic. UNC is a public academic medical center that includes a matrix NCI-designated Comprehensive Cancer Center and affiliated community oncology clinics. UNC serves a patient population that is ~ 33% rural and 20% Non-Hispanic Black/African American.

### Study design

The study will use a parallel pilot randomized controlled trial design and collect preliminary data on implementation and effectiveness outcomes. Patients will be 1:1 randomized to the 12-week STRONG program versus usual care and complete study assessments at baseline, 1 month, 3 months (end of intervention), and 6 months. The protocol is reported in accordance with the SPIRIT 2025 guidelines and Table 1 provides a study timeline [68]. Data will also be collected from healthcare providers (e.g., dietitians, physicians, nurses) and caregivers who support implementation. The trial is designed to be pragmatic and has broad inclusion criteria and implementation is integrated within existing care teams and workflows [61].

**Table 1 Tab1:**
[figure not shown]
Study timeline: Schedule of enrollment, interventions, and assessments

### Using the theoretical domains framework to develop a patient-mediated implementation strategy

The Theoretical Domains Framework (TDF) identifies the psychological, social, and environmental determinants that affect behavior change and implementation of evidence-based care [69–71]. The study team conducted a systematic review and qualitative research with patients, caregivers, and clinicians to identify key dietitian and patient behaviors to be targeted and potential determinants of behavior change, which were categorized based on the TDF. STRONG targets four primary barriers to nutrition counseling access and delivery including (1) lack of standardized protocols for dietitian referral and follow-up; (2) lack of patient-reported nutrition information to assist dietitians’ with monitoring malnutrition and tailoring nutrition counseling; (3) lack of patient awareness about the role of the dietitian in cancer care and the perceived value of nutrition care; and (4) lack of patient skills and resources necessary for engaging in and adhering to nutrition counseling recommendations. These barriers were mapped to the Theoretical Domains Framework (TDF) [69–71] and linked with the Behavior Change Technique Taxonomy [72], which informed the selection of implementation strategies.

The implementation logic model [73] for STRONG is presented in Fig. 1. The intervention includes an electronic health record (EHR) order for a standardized nutrition protocol that includes early nutrition counseling (first referral prior to treatment initiation) and ongoing follow up (bi-weekly visits for the first 12 weeks of treatment). The order set is designed to reduce complexity for the clinician by creating an automatic schedule of follow-up visits rather than ad-hoc scheduling of follow-up appointments that vary for each patient. Prior studies suggest that standardized protocols, particularly when available in the EHR, can increase the timeliness of referrals for evidence-based care [74–78]. 

**Fig. 1 Fig1:**
[figure not shown]
STRONG implementation logic model based on the theoritical domains framework

Referrals are more effective when paired with patient-mediated strategies that prepare the patient for engaging in the clinical encounter. Previous research has demonstrated that education about the purpose of a clinical visit and its potential value may increase uptake of nutrition and supportive care among cancer patients [50, 79]. The study team developed a question prompt list and a ‘what to expect from your dietitian visit’ handout to prepare patients for the dietitian visit. In other settings, question prompt lists have been effective for improving patient activation, communication self-efficacy and participation in clinical encounters (e.g., asking relevant questions) [80–84]. Patients will also receive a self-guided education booklet about eating problems and coping strategies specific to gastric and esophageal cancer to reinforce content that is provided as a part of nutrition counseling.

Research suggests that dietitians may need more patient-reported information to effectively monitor malnutrition and tailor nutrition counseling [51, 59, 85–88]. To address this, patient-reported information is collected from the patient including nutritional status (via the PG-SGA short-form [89, 90]), food intake and nutrition symptoms, and patient needs and preferences (e.g., food insecurity via Hunger Vital Sign [91]). Information collected is shared with a dietitian via a web-based dashboard and patients reporting food insecurity are provided with the option for referral to a nurse navigator or social worker. This information is collected to provide dietitians with data they may not otherwise have access to and help focus the nutrition counseling visits on patients’ needs and preferences (e.g., reviewing a food log from the prior week to identify opportunities for eating more nutrient dense foods when calorie goals are not being met). Prior studies have demonstrated that patient-reported information at the clinic encounter can improve the patient-centeredness of care and clinician’s ability to deliver timely and individualized feedback [92–95]. 

The long-term goal of the program is to improve access and consistency in the delivery of nutrition counseling, leading to improvements in service delivery (e.g., timeliness and patient-centeredness of nutrition care, hospital readmissions) and patient outcomes (e.g., nutritional status, quality of life, treatment tolerance, and survival) (Fig. 1).

### Trial approval, registration, and funding

The pilot trial is funded by the Department of Defense (DoD). The study protocol was approved by the Moffitt Institutional Review Board (IRB) of Record, Advarra, and a reliance agreement was established with the UNC IRB. The trial was registered on ClinicalTrials.gov (NCT06497569) prior to participant enrollment.

### Participant eligibility

Patients who meet the following criteria will be eligible: 1) ≥ 18 years of age; 2) diagnosis of gastric, esophageal, or gastroesophageal junction cancer; 3) planning to start systemic therapy and/or radiotherapy at the time of study enrollment; 4) have a treatment plan that includes surgery or definitive follow up at Moffitt or UNC; and 5) ability to provide informed consent in Spanish or English. Patients will be excluded if they have a hospice referral or plan for hospice enrollment at the time of study enrollment.

### Participant recruitment and consent

Study staff at both sites will screen the EHR for the minimum information necessary to identify potentially eligible patients with upcoming appointments and clinic staff will be encouraged to refer eligible patients to study staff. The study team will manage a Zoom channel that includes the dietitian and nursing team for communication and manage a study related inbox. At UNC, the Carolina Data Warehouse will develop a weekly automated screening list of potentially eligible patients from the UNC Health System (e.g., Lineberger Comprehensive Cancer Center and UNC affiliated community oncology sites). The study team will develop study flyers and a short video that describes the key components of the study to support recruitment.

Research staff who have completed human subjects and Health Insurance Portability and Accountability Act (HIPAA) training will perform screening and consent. Research staff will approach potentially eligible patients in clinic or contact them by phone or patient portal using an IRB-approved message to gauge interest. Study staff will introduce the study, assess interest, review key elements of informed consent, and obtain written informed consent from interested patients. A HIPAA authorization will be obtained from individuals who consent to participate in the study. A waiver of HIPAA authorization will be obtained for EHR screening and to retain a limited set of information on patients who decline to participate (e.g., sex, race/ethnicity, age, language preference, reason for decline) so that individuals who consent can be compared with individuals who declined to participate.

### Randomization

Patients (*N* = 80) will be 1:1 randomized to the STRONG program versus usual care. The study statistician will develop a randomization table using the randomization function in Stata (StataCorp. 2025. Stata Statistical Software: Release 19. College Station, TX: StataCorp LC.) that will be uploaded to REDCap^®^ (Research Electronic Data Capture). Randomization will be stratified based on cancer type and treatment modality (e.g., single versus multimodal treatment) to ensure groups are balanced on these factors, which may affect malnutrition risk. Block randomization (in variable block sizes of 4 and 6) will be used to maintain balance across groups and concealment. Outcome assessors and the study statistician will be blinded to group allocation.

### Intervention condition

Prior to treatment initiation, patients randomized to the intervention condition will meet with a study coordinator to receive and review the education brochure on common eating problems related to gastric and esophageal cancer and potential coping strategies, the question prompt list, and the handout on what to expect during a dietitian visit. Patients will be encouraged to bring a caregiver when available. Patients will also be asked about their preferences for recording nutrition-impact symptoms and food intake and be provided with an electronic option (food logging through Fitbit Inspire 3.0 and texting messaging tool) or a paper option (paper food diary). The research coordinator will review how to use either the electronic or paper option and use the teach-back method to ensure the participant understands how to use the tools. For patients using Fitbit to electronically record food intake, the study team will create a Fitbit account using a pseudonym (e.g., participant 1) and a study provided email address so that no identifying information is entered into the Fitbit app. The Fitbit app will be downloaded to the patients’ smartphone or a study-loaned device (e.g., cellularly enabled tablet) for patients who do not have a smart device or do not want to use their smart device for the study (e.g., limited data plan). The study coordinator will contact the clinic team, who will place the EHR order for the standardized nutrition counseling protocol. The protocol includes an initial dietitian visit prior to treatment initiation and bi-weekly follow-up for 12 weeks.

The first nutrition counseling appointment will be an hour in length after the patient has been discharged. The nutrition counseling will be delivered using the HIPAA-compliant version of Zoom videoconference; however, participants will have the option to schedule a phone visit or in-person visit if preferred. The content of the visit is based on nutrition guidelines in oncology and feedback gathered from clinicians, patients, and caregivers from qualitative research (Table 2) [28, 96–98]. Calorie and protein goals will be based on the European Society for Clinical Nutrition and Metabolism (ESPEN) guideline for clinical nutrition in cancer [28] and may be modified based on dietitian judgement (e.g., patient activity level, malnutrition severity). After the initial visit, the patient will meet with the dietitian on a bi-weekly basis. Follow-up visits will be approximately 30 min. Patients will use the app (or paper log) between visits to log food intake and nutrition symptoms at least 3x a week (non-consecutive days) and complete a malnutrition screening (PG-SGA short form [89, 90]) monthly. The intervention will last for the first 12 weeks (3 months) of treatment (when nutrition impact symptoms often increase in severity) [99, 100]. Guidance from NCI and prior studies of dietary assessment suggest that 3 days of non-consecutive food records is sufficient for accurately estimating food intake and reduces participant burden (compared with daily food records) [101, 102]. Therefore, we will encourage patients to log food intake and nutrition symptoms 3 days a week rather than daily. Dietitians will be given access to a dashboard that displays patient-reported information (e.g., malnutrition screening, food intake, nutrition impact symptoms). Visits will be documented in the EHR, which contains a template that covers key visit topics (e.g., nutrition history, food preferences).

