## Discussion

Pilot studies play a critical role in implementation research by ensuring that strategies and proposed study methods are feasible prior to conducting a larger and more costly definitive trial [135]. This pilot study will assess the feasibility of a patient-mediated implementation strategy to improve nutrition care delivery for esophageal and gastric cancer patients, who have a high burden of malnutrition [1–6]. The study is timed to deliver support to patients during neoadjuvant therapy prior to surgery, when nutrition care plays a pivotal role in long-term outcomes [44–47]. In the future, we aim to expand the program to individuals diagnosed with metastatic gastric and esophageal cancer who are receiving palliative chemotherapy, who may also greatly benefit from nutrition counseling. There has been limited research on implementation strategies designed to overcome barriers to delivering nutrition care during cancer treatment [136]. Additionally, there has been limited research on patient-mediated implementation strategies as an approach to increase evidence-based care delivery [66]. Positive findings from this line of research could expand the reach of evidence-based nutrition care during cancer treatment and improve patients’ nutritional status, quality of life, treatment tolerance, and survival.

**Table 2 Tab2:** Nutrition counseling content

Section	Content
Nutrition assessment	Detailed review of weight history, food intake, physical function, nutrition-impact symptoms, micronutrient deficiencies, medical history related to nutrition, treatment plan, relevant labs
Social needs	Screening for food insecurity and other barriers to nutrition
Food preferences	Discussion about foods individual typically eats, cultural, religious, or other dietary preferences
Physical activity	Review of physical activity
Goal setting and values clarification	Determine patient goals for improving nutrition and/or function and motivation for behavior change (e.g., quality of life)
Energy and protein requirements	Estimate requirements for calorie and protein intake
Nutrition counseling and education	Provide patient with dietary strategies based on nutrition problems (e.g., meal planning with nausea), recommended interventions (e.g., supplements, referrals), and education as needed (e.g., high quality protein sources)
Follow up	Review next steps, remind patient of what should be done between visits (e.g., food and symptom diary) and timing of next appointment

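### The Intervention condition section gives two timings for the first dietitian visit, so the number of scheduled visits behind the counseling-adherence benchmark is not fixed

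*Protocol article*

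**What the plan says.** The protocol article describes the first dietitian visit twice in its Intervention condition section, in consecutive paragraphs.

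- The first paragraph ends its account of the EHR order with: "The protocol includes an initial dietitian visit prior to treatment initiation and bi-weekly follow-up for 12 weeks".
- The second paragraph opens with: "The first nutrition counseling appointment will be an hour in length after the patient has been discharged".

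Four other statements bear on the timing:

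- The section on the theoretical domains framework describes "early nutrition counseling (first referral prior to treatment initiation) and ongoing follow up (bi-weekly visits for the first 12 weeks of treatment". Its early component is a referral, not a visit.
- The Intervention condition section spaces the later visits from the first one: "After the initial visit, the patient will meet with the dietitian on a bi-weekly basis".
- The same section ties the duration to treatment: "The intervention will last for the first 12 weeks (3 months) of treatment".
- Under Participant eligibility, patients are "planning to start systemic therapy and/or radiotherapy at the time of study enrollment". The Discussion adds: "The study is timed to deliver support to patients during neoadjuvant therapy prior to surgery".

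**The concern.** Both statements are operative rules for the same appointment. They agree only if the discharge comes before treatment starts, and the article describes no such event. Inpatient status is not an eligibility criterion, and recruitment takes place in clinic, by phone or through the patient portal. The one step in the described pathway that would naturally end in a hospital discharge is surgery, which comes after the period in which support is meant to be given.

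What is at stake is the visit count. Later visits are spaced from the first visit, while the intervention period is set by treatment. If the first visit moves, either fewer visits fit in the period or the series runs past its end. Table 3 requires at least 70% of patients to attend the majority (3/4) of dietitian visits, and counseling adherence is one of the feasibility outcomes that are primary in this pilot. The denominator of that benchmark is not fixed until the first visit has one anchor.

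**Working it through.** The article states no visit total, so there is no figure to reproduce. The check compares the statements and then counts visits.

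**Can the two statements be reconciled from the text?**

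| Meaning of discharge | Fits a first visit before treatment? | Described in the article? |
|---|---|---|
| Leaving a clinic appointment | Yes | No |
| End of an admission before treatment | Yes | No |
| End of an admission during treatment | No | No |
| Discharge after surgery | No | Surgery is part of the pathway, but the Discussion places support before it |

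The two meanings that would remove the conflict are not stated. The surgical meaning also contradicts the Discussion.

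**How does the visit count depend on the timing?**

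Inputs from the Intervention condition section: one initial visit, follow-up every 2 weeks, and a 12-week intervention period. Let d be the treatment week of the first visit, with d = 0 standing for a visit at or just before treatment start. The article gives no value for d after a discharge, so the values from 2 to 8 below are assumptions.

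*Reading 1: the window is fixed to the first 12 weeks of treatment.*

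Visits in the window: V = 1 + floor((12 − d)/2). Visits needed under the 3/4 rule, read as a proportion of the visits scheduled: the smallest whole number not below 0.75 × V.

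| d (weeks) | V | 0.75 × V | Visits needed |
|---|---|---|---|
| 0 | 1 + 6 = 7 | 5.25 | 6 |
| 2 | 1 + 5 = 6 | 4.50 | 5 |
| 4 | 1 + 4 = 5 | 3.75 | 4 |
| 6 | 1 + 3 = 4 | 3.00 | 3 |
| 8 | 1 + 2 = 3 | 2.25 | 3 |

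If the discharge came after week 12, no visit would fall in the window.

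*Reading 2: follow-up runs 12 weeks from the first visit.* The sentence "The protocol includes an initial dietitian visit prior to treatment initiation and bi-weekly follow-up for 12 weeks" allows this. Then V = 1 + 12/2 = 7 for every d, and 6 visits are needed. No visit is lost, but the last one falls in treatment week d + 12. For d = 4 that is week 16, beyond the period stated in "The intervention will last for the first 12 weeks (3 months) of treatment".

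**Which measures depend on the first visit?**

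- Counseling adherence (Table 3): yes, through the number of visits scheduled.
- Referral timeliness (Secondary effectiveness outcomes): no. The example given runs from diagnosis to first referral.
- Surveys (Study assessment schedule): no. They are set at baseline, 1, 3 and 6 months.
- Fidelity (Secondary implementation outcomes and Table 3): not counted from the first visit. It concerns which counseling elements were delivered, and how much.
- Sample size and precision (Sample size considerations): no visit count enters.

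**The case against.** The strongest reply is that the discharge clause is one stray phrase in a condensed article. Everything around it points to counseling early in treatment and before surgery. Delivery runs through a single EHR order set that creates the follow-up schedule automatically, and nothing shows that site documents repeat the clause.

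Much of this stands. There is no evidence that the two sites would deliver different schedules, and the clause may be a drafting leftover. But the clause is a positive statement that conflicts with the paragraph before it, not a detail left to the full protocol, and the article does not say which statement governs.

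A reader might also infer more than the text supports:

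- *That the theoretical domains framework section also fixes the visit before treatment.* Its words are "first referral prior to treatment initiation". It is in keeping with early timing but does not date the visit.
- *That a delay makes the attendance benchmark unattainable.* With a 4-week slip, 5 visits remain, while 6 would be needed out of 7. That result needs both an assumed delay and a denominator held at 7, which Table 3 does not state. If the denominator follows the schedule, 4 of 5 suffices. If follow-up runs from the first visit, all 7 visits remain.
- *That every STRONG patient would be seen late.* The rule applies to the whole arm (80/2 = 40 patients), but no admission is required, so the article gives no basis for a delay in each of them.
- *That timeliness, fidelity and the 3-month outcome also lose their start point.* None of them is counted from the first visit. A later visit could change how much counseling comes before the 3-month survey, but not when that survey is due.

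**Conclusion.** The contradiction is real as written. The same appointment is placed before treatment in one paragraph and after an undefined discharge in the next, and nothing in the article reconciles the two.

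The statistical consequence is narrow. The number of scheduled visits, and with it the 3/4 counseling-adherence benchmark, is undetermined: from 7 down to 3 visits for assumed first visits at treatment weeks 0 to 8 if the window is fixed to treatment, or 7 throughout if follow-up runs from the first visit. These counts illustrate the dependence and do not predict any delay. They assume strict two-week spacing and the 3/4 rule read as a proportion of scheduled visits. No estimate, survey time point, sample size or precision figure changes. The correction is still worth making, because it concerns the core intervention step and costs little.

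**What to change.** - Reconcile the two statements in the Intervention condition section so that the first visit has one stated anchor, and check the result against the referral wording in the theoretical domains framework section. If a discharge is meant, name the event. Which timing applies is for the clinical team to decide.
- State whether bi-weekly follow-up ends 12 weeks after the first visit or at treatment week 12, and use that to define the number of scheduled visits for the counseling-adherence benchmark in Table 3.
- Check that the site documents and the EHR order set carry the same wording.

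The cost is about one corrected sentence and one added definition, with a notice to the sites. An amendment is needed only if the approved site documents carry the conflicting clause.
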